## Abstract

**Background:**

The School Fruit and Vegetable Scheme (SFVS) is an important public health intervention. The aim of this scheme is to provide a free piece of fruit and/or vegetable every day for children in Reception to Year 2. When children are no longer eligible for the scheme (from Year 3) their overall fruit and vegetable consumption decreases back to baseline levels. This proposed study aims to design a flexible multi-component intervention for schools to support the maintenance of fruit and vegetable consumption for Year 3 children who are no longer eligible for the scheme.

**Method:**

This study is a cluster randomised controlled trial of Year 2 classes from 54 primary schools across England. The schools will be randomly allocated into two groups to receive either an active intervention called Project Tomato, to support maintenance of fruit intake in Year 3 children, or a less active intervention (control group), consisting of a 5 A DAY booklet. Children's diets will be analysed using the Child And Diet Evaluation Tool (CADET), and height and weight measurements collected, at baseline (Year 2) and 18 month follow-up (Year 4). The primary outcome will be the ability of the intervention (Project Tomato) to maintain consumption of fruit and vegetable portions compared to the control group.

**Discussion:**

A positive result will identify how fruit and vegetable consumption can be maintained in young children, and will be useful for policies supporting the SFVS. A negative result would be used to inform the research agenda and contribute to redefining future strategies for increasing children's fruit and vegetable consumption.

**Trial registration:**

Medical Research Council Registry code G0501297

## Background

The United Kingdom Government's national 5 A DAY programme forms part of the strategy to raise awareness of the health benefits of fruit and vegetable consumption, and to improve access to fruit and vegetables. One aspect of the 5 A DAY programme is the School Fruit and Vegetable Scheme (SFVS) which provides a free piece of fruit or vegetable to children aged four to six years each school day. The scheme has been rolled out nationally during 2004, and involves distributing approximately 440 million pieces of fruit or vegetable each year to over two million children in 18,000 schools across England. The Department of Health has agreed to continue funding the scheme with a further £77 million investment.

A formal evaluation of the SFVS was carried out by our team in 2004[1]. This evaluation was conducted in schools from two areas – the North East and a matched comparison sample from Yorkshire and Humberside; ninety-eight schools in total. Children were assessed at baseline prior to the introduction of the SFVS and again following introduction of the scheme in the North East with Yorkshire and Humberside acting as comparison schools. Results from this evaluation of the SFVS suggest that most children do not consume enough fruit and vegetables[2]. In particular, the evaluation showed that children significantly increased their fruit and vegetable intake following the introduction of the SFVS by 0.5 portion/day. However, once children move from Year 2 into Year 3 when free fruit is no longer available consumption returns to baseline.

The SFVS is one of the largest public health interventions in Britain in recent years. It is important to assess both the longer term impact on children's diets and the sustainability of the scheme in schools with a focus on social inequalities. It is also important to try to maintain fruit and vegetable consumption once the children enter Year 3 and are no longer eligible for the SFVS.

Interventions, apart from the SFVS, have been shown to increase fruit and vegetable intake in children [3-5]. A review by Ciliska et al[6], on the effectiveness of community interventions for increasing fruit and vegetable consumption in children, stated that the most successful interventions gave clear messages, incorporated multiple reinforcing strategies, involved the family, were more intensive, provided over a longer period of time (i.e. not just one or two contacts) and were based on a theoretical framework

The strategies developed and tested in this intervention will be based upon these successful elements and built on a framework related to maintenance of health behaviour. In contrast to social cognition models that focus on initiation of health behaviour, maintenance of health behaviour theories state the need to understand factors determining maintenance over prolonged periods of time. Five theories that suggest factors important in the decision to initiate behaviour change will form the theoretical basis for development of a model suitable for behaviour maintenance in children. These theories include the role of satisfaction; self-efficacy; social support; self-determination theory; and the relapse prevention model [7-11].

### Aims of the study

• To develop an intervention aimed at maintaining fruit and vegetable consumption in Year 3 children (aged 7–8 years)

• To conduct a randomised controlled trial on the effectiveness of the intervention in maintaining fruit and vegetable intake compared with a minimal intervention.

## Method/Design

### Population

The schools for this study will be randomly selected from a sample of 130 chosen to take part in a national cross-sectional study to describe fruit and vegetable intake in Year 2 children. These schools will be chosen to be representative in terms of ethnicity, deprivation, achievement, and region of England, and will be stratified on ethnicity measured by percentage non-white in each school (split into thirds), deprivation measured by the percentage of free school meals at each school (split into fifths), achievement measured by performance at key stage 1 (split into fifths) and region (North, Midlands and South of England). The inclusion criteria for this sample will be all of schools containing pupils in years 2–4, with a minimum year group size of 15 pupils. The exclusion criteria will be small schools with less than 15 pupils per year group; independent schools, special schools, schools without all three years 2–4, and schools that are or have previously participated in National Foundation for Educational Research (NFER) projects or have participated in previous SFVS projects.

### Sample size

From the nationally representative sample, a sub-set of schools will be recruited into the intervention trial. Cluster randomisation will be used, randomising at the school level, as the intervention will involve whole lesson plans and school-level policies. A sample of 25 children (one Year 2 class) from each school, will give a design effect of approximately 3.4 to take account of the cluster randomisation. To have 90% power to detect a 0.5 portion difference in fruit intake, 500 children per group are required, i.e. about 20 schools in each group. Based on results from our initial evaluation of the SFVS, 75% who completed CADET at baseline also completed the follow up CADET. To allow for this margin of safety, 27 schools per group will be selected in each group, i.e. 54 schools in total. The size of effect the study is powered to detect (one half of a portion of fruit/vegetable) was chosen because it was considered the smallest improvement in intake that was worthwhile detecting with an achievable sized sample, and considering the nature of the intervention.

### Randomisation

To ensure balance on important potential confounders within the trial, block randomisation within strata will be used, stratifying on measures of ethnicity (% non-white) and deprivation (% Free School Meals), both split at the median. Whilst we would like to stratify on variables such as region and achievement, there are not enough schools to give large enough strata to do this. Block randomisation will use block sizes of two because allocation will take place in one go, so there will be no opportunity for prediction of which group the schools will be in.

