### Study procedure

Eligible schools will be sent a letter, additional information and a consent form inviting them to take part in the study. Consenting schools will then be contacted to arrange an appropriate day to collect baseline information from the children. A study recruitment form will also be sent to the schools/Year 2 teachers. The teacher will use this form to record which children obtained parental consent and which children were absent on the CADET day. Parental, opt-out consent will be obtained prior to data collection. Baseline dietary information using CADET and anthropometric measures of the children will be collected by the fieldworker in the school.

Following baseline data collection, the randomly selected schools for the trial will be sent a letter informing them whether they are in the active or less intensive intervention. The allocation sequence will be generated by the trial statistician. All schools will be allocated at the same time. Time between notification of allocation and receiving the first intervention material will be kept to a minimum to minimise withdrawals at that stage.

Blinding of the schools to their intervention group will not be possible because of the nature of the intervention. Fieldworkers will be blinded to the allocation of schools to the intervention and control arms of the study. Schools will be followed up 18 months later when the sample of children are in year 4 (aged 8–9 years). They will have further measures of diet using CADET and anthropometric measures taken.

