### Statistical Analysis

A random intercepts model of child-level outcomes will be used allowing for the hierarchical structure of the data caused by cluster randomisation: child within school. An extra level for the class is unnecessary because only one class is included from each school. MLwiN[15] will be used for this analysis. The fixed effect for the intervention group will be included in the model as a single covariate.

Balance of school and child-level variables between the two intervention groups will be assessed at baseline. This will be carried out with the following variables i) at school level: percentage of children with English as an additional language, percentage of non-white children, percentage of children with free school meals eligibility and percentage defined as having special educational needs ii) and at child level: sex, age and each of the primary and secondary child-level outcomes.

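### Region and key stage 1 achievement are left to chance at allocation, although sorted pairs or constrained randomisation could balance them cheaply with the same 54 schools

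*Protocol article*

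**What the plan says.** The Sample size section plans "27 schools per group will be selected in each group, i.e. 54 schools in total". The Randomisation section sets out to balance important potential confounders. It uses blocks within strata formed by percentage non-white and percentage free school meals, each split at the median, which makes four strata. On two further factors it says: "Whilst we would like to stratify on variables such as region and achievement, there are not enough schools to give large enough strata".

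Three other statements bear on this.

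- **Population:** the trial schools come from a sample of 130 that is itself stratified on region (three levels) and key stage 1 performance (fifths), among other factors.
- **Randomisation and Study procedure:** "Block randomisation will use block sizes of two because allocation will take place in one go", and "All schools will be allocated at the same time".
- **Statistical Analysis:** the random intercepts model is described with intervention group as its only covariate. The school-level balance check covers "percentage of children with English as an additional language, percentage of non-white children, percentage of children with free school meals eligibility" and special educational needs. The child-level check covers sex, age and every primary and secondary child-level outcome. Region and achievement are in neither list.

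**The concern.** The plan says it wants balance on region and achievement and gives it up for one reason, the size of the strata. That reason belongs to cross-classified stratification and not to balancing in general. When every school is allocated in one run, and the covariates are already held, the statistician can pair similar schools or restrict the draw to well-balanced allocations. Neither option is mentioned.

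What is at stake is precision and credibility. With 27 schools per arm, a sizeable chance imbalance on a school-level factor is not rare. By the plan's own design effect, most of the variance of the effect estimate lies between schools. The opportunity also passes once the allocation has been run.

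**Working it through.** **1. The plan's number of schools.** The section states "500 children per group are required, i.e. about 20 schools in each group". 500/25 = 20 schools per group; 20/0.75 = 26.7, rounded up to 27; 2 × 27 = 54. The stated figure reproduces.

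**2. Is the stated reason correct for crossed strata?** Schools per cell:

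| Strata | Cells | Schools per cell |
|---|---|---|
| Ethnicity × deprivation (plan) | 4 | 54/4 = 13.5 |
| plus achievement at the median | 8 | 54/8 = 6.75 |
| plus region | 12 | 54/12 = 4.5 |
| plus both | 24 | 54/24 = 2.25 |
| plus region and achievement in fifths | 60 | 54/60 = 0.9 |

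Yes. In simulation, 24 cells gave arm totals differing by 4 or more schools in 39% of allocations and upset ethnicity or deprivation by 4 or more in 28%. With 60 cells these were 55% and 63%.

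**3. Chance imbalance, by formula.** Assume 18 of the 54 schools are in a given region. The number in one arm is hypergeometric (54, 18, 27):

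- 12:6 or worse: 2 × P(X ≥ 12) = 0.148
- 13:5 or worse: 2 × P(X ≥ 13) = 0.042

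For a standardised achievement score, the arm difference has SD √(4/54) = 0.272. The chance that it exceeds 0.5 SD is 2 × [1 − Φ(0.5/0.272)] = 0.066.

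**4. The planned scheme and the alternatives, by simulation.** Assumptions: 18 schools per region, a normal achievement score, and independent factors unless stated.

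- *Plan (four strata, random blocks of two):* at least one of the three regions splits 12:6 or worse in about 32% of allocations. The largest regional difference averages 4.2 schools (95th percentile 8). Achievement differs by more than 0.5 SD in about 7%. If achievement correlates 0.5 with free school meals, which the strata already balance, this is about 5%; at 0.7 it is about 3%.
- *Same strata and blocks, schools sorted by region and then achievement before pairing:* the 32% falls to about 1%. A pair from one region adds nothing to the regional difference, so only pairs that straddle two regions and unpaired schools can. For achievement the 7% falls to about 3%; over moderate correlations, about 4–7% falls to about 2–3%.
- *Constrained randomisation within the same strata (200 candidates, one drawn at random from the best 10%):* the largest regional difference averages 1.7 schools (95th percentile 2). The mean absolute achievement difference is 0.12 SD, against 0.22 under the plan. Ethnicity and deprivation balance is unchanged.

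**5. Between-school share of the variance.** One class of 25 "will give a design effect of approximately 3.4 to take account of the cluster randomisation". The implied ICC is (3.4 − 1)/24 = 0.10, and the between-school share is 25 × 0.10/3.4 = 74%. At 75% retention (18.75 children per school) it is 0.10/(0.10 + 0.90/18.75) = 68%.

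**6. Possible effect on the estimate (illustration).** The article gives neither an SD nor an alpha. The target is "To have 90% power to detect a 0.5 portion difference in fruit intake"; with two-sided 5% and a design effect of 3.4, 500 per group implies an SD of about 1.32 portions. The between-school SD is then 1.32 × √0.10 = 0.42. If achievement explains 5–20% of between-school variance, a 0.5 SD imbalance shifts the estimate by 0.5 × 0.42 × √0.05 = 0.05 to 0.5 × 0.42 × √0.20 = 0.09 portion. The standard error is √(2 × 3.4 × 1.32²/500) = 0.15.

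**The case against.** The best defence is that nothing in the Randomisation section is false. The sentence is about stratifying, the cell counts bear it out, and stratifying on two confounders while leaving two to chance is a legitimate, openly stated choice. This stands: the point is an improvement that serves the plan's own aim, not an error or a contradiction.

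A reader might go further and infer that the arms will be unbalanced and the comparison biased. The document does not support that. Randomisation balances both factors in expectation, and the school random intercept carries residual between-school variation into the standard error, so chance imbalance is already reflected in the confidence interval.

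A reader might also infer that an imbalance would go wholly unnoticed. That is too strong as well. The baseline check covers the child-level outcomes, including fruit and vegetable intake, and would partly reveal an imbalance that mattered. The article is also condensed, so further covariates or table rows may be set out elsewhere.

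Materiality is the remaining objection, and it stands in part. The article does not say how strongly region or achievement predicts intake, and the illustrative shift of 0.05–0.09 portion is small beside the 0.5 portion target. Nor is the change free, since balancing factors should be reflected in the analysis. None of this explains why a balance the team wants should be given up when the stated obstacle does not apply to the alternatives.

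**Conclusion.** The point holds as a cheap improvement. Too few schools is a sound reason against crossing four factors, but not against pairing similar schools or constraining the draw. The clear gain is for region; the gain for achievement is modest, and smaller still if achievement tracks free school meals closely. These figures rest on 18 schools per region and on assumed covariate distributions, which the article does not give for the 54 schools. What is gained is precision and face validity, in proportion to the unknown prognostic strength of the two factors. The validity of the planned comparison is not in question.

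**What to change.** Before the single allocation run:

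1. Keep the four strata. Within each, sort schools by region and then by key stage 1 achievement, form the blocks of two from neighbours, and randomise within each pair. Alternatively, use constrained randomisation on all four factors with the algorithm and acceptance rule written down in advance, and check that it is not over-constrained, so that no two schools are forced together or apart.
2. State how unpaired schools are allocated. With two median splits giving 27:27, strata have sizes a, 27 − a, 27 − a and a, so two of the four have an odd number.
3. Add region and achievement to the model as school-level covariates, and to the school-level balance table.

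The cost is a small change to the allocation script and about 3 school-level degrees of freedom (2 for region, 1 for achievement). No extra schools or data are needed.

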### Study procedure

Eligible schools will be sent a letter, additional information and a consent form inviting them to take part in the study. Consenting schools will then be contacted to arrange an appropriate day to collect baseline information from the children. A study recruitment form will also be sent to the schools/Year 2 teachers. The teacher will use this form to record which children obtained parental consent and which children were absent on the CADET day. Parental, opt-out consent will be obtained prior to data collection. Baseline dietary information using CADET and anthropometric measures of the children will be collected by the fieldworker in the school.

Following baseline data collection, the randomly selected schools for the trial will be sent a letter informing them whether they are in the active or less intensive intervention. The allocation sequence will be generated by the trial statistician. All schools will be allocated at the same time. Time between notification of allocation and receiving the first intervention material will be kept to a minimum to minimise withdrawals at that stage.

Blinding of the schools to their intervention group will not be possible because of the nature of the intervention. Fieldworkers will be blinded to the allocation of schools to the intervention and control arms of the study. Schools will be followed up 18 months later when the sample of children are in year 4 (aged 8–9 years). They will have further measures of diet using CADET and anthropometric measures taken.

### Study intervention

Using the theoretical framework of maintenance of health behaviour the Project Tomato intervention will employ the following principles – familiarisation, repetition, activities, modelling, and environment (FRAME). Research has shown consistently that the more children are exposed to tasting fruit and vegetables (*familiarisation*) in positive and supportive *environments*, the more willing they are to try them and the more likely they are to like and accept them as a regular component of their diet. Research has also shown that *repeated *exposure to fruit and vegetables encourages children to eat them. Children model their eating behaviour on those around them. This means positive peer and adult role *models *are vital in getting children to accept fruit and vegetables as a regular and likeable part of the diet. Another key finding from research shows that the more children interact with these foods through *activities *such as growing, cooking and tasting, the more likely they are to like and accept them. In some cases, school provides the only opportunity for children to learn about the importance of these foods into their diet [7-11].

The intervention consists of a number of core elements together with some customised elements to meet the needs of each school. The duration of the intervention will be 10 months. The customised elements will be selected and agreed with schools according to their existing cooking or growing facilities, and programmes relating to fruit and vegetables. The final tailored intervention package will be agreed with staff at each school.

### Control Group

An easy to read coloured 5-A Day booklet "Just eat more fruit and veg[12]" will be provided to control schools along with links to relevant websites: one per pupil to send home. At the end of the study the control schools will also be offered access to the full intervention materials if they requested them.

### Outcome measurements

#### Primary outcome

The primary outcome will be the ability of the intervention (Project Tomato) to maintain consumption of fruit and vegetable portions following the exit of children from the SFVS over 18 months compared to the control group.

### Secondary outcomes

#### Diet

Intake of key nutrients including; total energy(MJ/day), fat(g/day), salt(g/day), sugars (g/day), carotene mg/day), and vitamin C (mg/day) will be assessed using the CADET, which has been validated in an ethnically diverse population[13].

#### Behavioural

Children's attitude to fruit and vegetable consumption as measured by a set of ten questions embedded in CADET[14].

#### Anthropometric measures

Weight (kg) measured using standardised procedures and equipment. Body mass index (kg/m^2^) based on weight (as above) and height measured using standardised procedures and equipment following training from the Child Growth Foundation, London.

#### School level measures

Involvement of schools in promoting consumption of fruit and vegetables (number of lessons devoted to learning about fruit and vegetables, school food policy, resources, involvement in national/local initiatives) will be measured using a school questionnaire. Assessment of parents/carers involvement in promoting consumption of fruit and vegetables among pupils will be undertaken using questionnaires.

